### Statistical analysis

#### Baseline comparability

Quantitative variables will be described as mean ± standard deviation (SD) when normally distributed, or as median (IQR) if non-normally distributed, and qualitative variables as number (percentage). The baseline characteristics of both groups will be compared by univariate analysis (chi square or Fisher’s exact test for qualitative variables, Student’s t-test, Mann-Whitney U test or ANOVA for quantitative variables, as appropriate).

#### Primary objective

The primary analysis will be on an intention-to-treat basis. Event-free catheter survival will be compared between groups using the log rank test. Time zero is defined as the time of randomization, and the time to withdrawal of the first non-tunneled hemodialysis catheter (event-free catheter survival) will be calculated starting from randomization for the analysis of the primary endpoint. Patients will be censored in case of scheduled withdrawal of the catheter, or death. Then, multiple Cox regression analysis will be performed as appropriate, to take into account any potential imbalances in potential confounders between groups. Treatment effects will be expressed as HRs with 95% CI. *P* values will also be provided. A per-protocol analysis will also be performed, using the same techniques. For the per-protocol analysis, patients will be grouped according to the treatment actually received.

An interim analysis is planned once 50% of the expected number of patients has been included (after inclusion of 200 patients). The time between randomization and withdrawal of the catheter will be described in both groups and compared using the log rank test, with an alpha risk fixed at 0.0001 (according to the method proposed by Peto *et al*. [42], to avoid inflating the alpha risk of the main analysis at the end of the study).

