## Background

The incidence of acute kidney injury (AKI) varies according to the populations studied and the definition used, but it is estimated to be around 10 to 20% in patients admitted to the intensive care unit (ICU) [1–3]. The cause of AKI is most commonly acute tubular necrosis occurring in the context of shock (septic and/or cardiogenic), or drug toxicities (such as aminoglycosides or contrast medium). The pathophysiology of AKI is well established, and includes vascular, medullar and tubular injury leading to a reduction in the rate of glomerular filtration, and ultimately, anuria [4]. Renal replacement therapy (RRT) can be required, depending on the AKI etiology and comorbidities, particularly pre-existing renal insufficiency. In one observational study carried out among almost 30,000 ICU patients, the rate of RRT was around 4% [3], but rates as high as 70 to 80% have been reported in patients with shock [5–7]. Mortality in the ICU ranges from 15 to 25%, but can reach 50 to 60% in patients with AKI [3, 8].

Venous catheters are currently the preferred vascular access method for patients with AKI requiring extracorporeal RRT [9, 10]. In critical care, non-tunneled catheters represent standard practice. Despite the vast progress in the management of AKI and high-quality catheter practices [11–13], vascular access remains the weak link in the chain of RRT and contributes to increased morbidity in hemodialysis patients, particularly through catheter dysfunction (stenosis and/or thrombosis) and infection.

Strategies to prevent hemodialysis catheter dysfunction and infection include catheter locks, which are generally either heparin or citrate. The principle of the catheter lock is to instil an anticoagulant solution into the lumen of the branches of the hemodialysis catheter after each RRT session, leaving them in place until the next session.

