### Study endpoints

#### Primary endpoint

The primary endpoint is the duration of event-free survival of the first non-tunneled dialysis catheter, defined in days as the time from randomization to catheter withdrawal, whatever the reason (infection, thrombosis, leakage or deteriorated catheter and unintentional or accidental catheter removal).

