### Sample size calculation

The sample size was calculated using PASS software (version 11, Kayesville, Utah, United States), based on several assumptions. The study by Hermite *et al*. [41] compared the event-free survival of catheters with citrate locks versus saline solution in ICU patients with an indication for extracorporeal RRT. In this study, the median duration of catheter survival with citrate locking solution was 12 days (interquartile range (IQR): 8 to 17], versus six days [3–10] for catheters locked with saline solution (hazard ratio (HR): 2.12, 95% confidence interval (CI): 1.32 to 3.4), *P* = 0.0019). The study by Weijmer *et al*. [15] reported an RR of 0.69 (95%CI: 0.44 to 1.08), *P* = 0.11) for premature withdrawal of non-tunneled, uncuffed catheters with citrate versus heparin. On the basis of these findings, in the prudent hypothesis of a reduction of 25% in the risk of catheter-related events (median of 12 days in the citrate group versus nine days in the heparin group), at an alpha risk of 5% and a beta risk of 20%, a total of 366 patients (183 per group) is required. Accounting for possible crossovers between groups (less than 5% switching from heparin to citrate) due to heparin-induced thrombocytopenia, and allowing for patients lost to follow-up, the final sample size is calculated to be 386 patients (193 patients included per group).

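### The primary event is catheter withdrawal for any reason in one section, but scheduled withdrawal and death are censored in another: the definition needs reconciling, the hazard ratio is cause-specific, and censored curves would overstate actual catheter failure

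*Protocol article*

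**What the plan says.** The Primary endpoint section of the protocol article defines event-free survival of the first catheter as "the time from randomization to catheter withdrawal, whatever the reason (infection, thrombosis, leakage or deteriorated catheter and unintentional or accidental catheter removal". Every reason in that list is unplanned. Neither scheduled removal nor death appears in it.

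The Primary objective section, under Statistical analysis, then states: "Patients will be censored in case of scheduled withdrawal of the catheter, or death". The analysis is set out in two sentences: "Event-free catheter survival will be compared between groups using the log rank test" and "Treatment effects will be expressed as HRs with 95% CI". No competing-risk method is named. No Kaplan-Meier curve or median is specified for the final analysis, and the interim paragraph says only that time to withdrawal will be described and compared by log-rank.

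Three other places bear on the point:
- Sample size calculation plans on a "median of 12 days in the citrate group versus nine days in the heparin group".
- Background says that ICU mortality "can reach 50 to 60% in patients with AKI", without a time frame.
- Patient management has catheters taken out before discharge where possible, so scheduled removal is a routine end to a catheter's life. Its rate is not given.

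**The concern.** Two linked problems arise.

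First, a catheter removed because it is no longer needed is an event if the endpoint definition is read literally, and a censored observation under the analysis rule. Those two readings give different event counts and different hazard ratios for the primary result.

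Second, once a catheter has been removed on schedule or the patient has died, unplanned withdrawal can no longer happen. Censoring such patients produces curves that describe a setting in which nobody dies and no catheter is removed on schedule. The endpoint is expressed as a duration in days and the planning is done in medians, so readers may take such curves or medians as the real fate of the catheters.

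The competing events might also depend on treatment. Background cites the bleeding risk of heparin, and reports less bleeding and fewer deaths from catheter-related bacteremia with citrate in an earlier randomized study. A patient who died of such a bacteremia with the catheter in place would be censored here as free of the event. A cause-specific hazard ratio alone would not show that.

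**Working it through.** **1. The two sections side by side**

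| How the first catheter's course ends | Primary endpoint, read literally | Primary objective |
|---|---|---|
| Infection, thrombosis, leakage or damage, accidental removal | event | event |
| Scheduled removal | event | censored |
| Death with the catheter in place | not addressed | censored |

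The second row is the conflict.

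**2. Inputs** (constant hazards per day; unrounded values carried through)
- Medians of 9 and 12 days, from Sample size calculation, taken as net medians for unplanned withdrawal (assumption). Heparin: ln 2/9 = 0.0770. Citrate: ln 2/12 = 0.0578. The ratio is 9/12 = 0.75, which reproduces the plan's stated 25% reduction.
- Death with the catheter in place: 50% by day 28. This is an assumption. The Background figure is an upper-range ICU mortality with no day-28 horizon, and it includes deaths after catheter removal. Hazard: −ln(0.5)/28 = 0.0248.
- Scheduled removal: 0.04 per day, equal in both arms (assumption; varied from 0 to 0.08).

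**3. What a censored estimate would show at day 28**

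1 − KM = 1 − exp(−28h)
- Heparin: 1 − exp(−28 × 0.0770) = 0.884
- Citrate: 1 − exp(−28 × 0.0578) = 0.802

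**4. What proportion of catheters would actually fail by day 28**

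CIF = h/(h + 0.0248 + s) × [1 − exp(−28(h + 0.0248 + s))], with s = 0.04
- Heparin: 0.0770/0.1418 × [1 − exp(−28 × 0.1418)] = 0.533
- Citrate: 0.0578/0.1225 × [1 − exp(−28 × 0.1225)] = 0.456

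Heparin over the range of s:
- s = 0: 0.0770/0.1018 × [1 − exp(−28 × 0.1018)] = 0.713
- s = 0.08: 0.0770/0.1818 × [1 − exp(−28 × 0.1818)] = 0.421

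The censored estimate stays at 0.884 throughout.

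A second parameterization fixes only the share of heparin catheters that end in scheduled removal or death. At a 30% share, the day-28 cumulative incidence is 67% (heparin) and 59% (citrate). At 50% it is 49% and 42%. The censored figures remain 88% and 80%.

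**5. Medians**

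The Kaplan-Meier medians stay at 9 and 12 days. With s = 0.04, heparin cumulative incidence reaches 50% at −ln(1 − 0.5 × 0.1418/0.0770)/0.1418, about 18 days. In the citrate arm it never does, because its ceiling is 0.0578/0.1225 = 0.471.

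**6. What the choice of reading changes**

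Take s = 0.04, 183 patients per arm and follow-up to the end of each catheter.
- Scheduled removal censored: 183 × (0.0770/0.1418 + 0.0578/0.1225) = 186 events, hazard ratio 0.75.
- Scheduled removal counted as an event, death still censored: 183 × (0.1170/0.1418 + 0.0978/0.1225) = 297 events, hazard ratio 0.0978/0.1170 = 0.84.

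**7. Does the log-rank test keep its level?**

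In 8,000 simulated trials per scenario, with competing shares of 30% and 50%, the type I error was 4.8% to 5.1%. That includes scenarios in which one arm's competing hazard was 0.75 times the other's.

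**The case against.** The strongest reply is that the text can be read consistently. The listed reasons are all unplanned, Sample size calculation speaks of catheter-related events, and the analysis rule says explicitly how scheduled withdrawal and death are handled. Together these point to time to unplanned withdrawal, loosely worded. That stands as the likely intention, but it does not remove the literal conflict in the definition of the primary event.

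A reader might go further and infer that the primary test is invalid, or that the trial's survival curves and medians will be wrong. The documents do not support either. Log-rank and Cox with competing events censored are a standard comparison of cause-specific hazards, and the simulated level is correct. The final analysis commits to a test and hazard ratios, not to curves or medians, and a condensed article may leave such displays to an analysis plan that is not shown.

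It is also fair that the illustration does not measure an error in this trial. The documents give neither the rate of scheduled removal nor the rate of death with the first catheter in place.

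The question of net benefit is partly covered, because mortality, transfused bleeding, dysfunction and infection are secondary endpoints. Investigator blinding limits allocation-driven timing of removal, and nothing in the text says that the lock changes that timing. Treatment-dependent censoring is therefore plausible but not shown.

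**Conclusion.** The point holds in a limited form and should be fixed. The definition of the primary event and the censoring rule disagree on scheduled withdrawal, and in the illustration the two readings give 186 events with a hazard ratio of 0.75 or 297 events with 0.84.

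Scheduled removal and death are competing events, and the article's own mortality figure makes death potentially common. The planned hazard ratio is therefore interpretable only as cause-specific, and a censored curve or median could not be read as actual catheter loss. Under the stated assumptions the day-28 overstatement is 88% against 53% for heparin and 80% against 46% for citrate. The true heparin figure runs from 71% to 42% as the scheduled-removal hazard goes from 0 to 0.08 per day.

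The direction of the overstatement does not depend on the chosen rates. Its size does, and it rests on constant hazards, on reading the planning medians as net medians, and on two competing rates that the documents do not supply. Nothing here shows that the primary test is wrong.

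**What to change.** - Reword the Primary endpoint section so that the event is unscheduled withdrawal for the reasons already listed, matching the censoring rule. Use the same wording for the interim comparison.
- Name scheduled withdrawal and death as competing events.
- Keep the log-rank test and Cox model, and label the hazard ratio cause-specific.
- Report Aalen-Johansen cumulative incidence by arm for unscheduled withdrawal, scheduled withdrawal and death, in place of censored curves or medians as the description of catheter fate.
- An all-cause sensitivity analysis (any withdrawal or death) is a reasonable supplement. It cannot replace the primary analysis, because competing events that the lock does not affect dilute the effect: in the illustration its hazard ratio is 0.1225/0.1418 = 0.86. A Fine-Gray model is optional.

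The cost is a change of wording, a few lines of code and slightly more reporting. Removal date and reason are already on the case report form, so no new data are needed. Trial status reports 191 patients recruited at submission and the interim comparison is set at 200, so the event should be settled before the arms are compared.

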#### Randomization procedure

Randomization will be performed directly through the secure Tenalea™ internet-based software (Formsvision BV, Abcoude, Netherlands) after identification of the investigator by a personal password, which will be communicated prior to initiation of the study. The treatment algorithms have been determined by the study statistician (Clinical Investigation Centre - Clinical Epidemiology/Clinical Trials (CIC-EC), Dijon, France). The allocation is based on a minimization technique taking into account the catheter insertion site (jugular or femoral), type of dialysis (continuous or intermittent) and Simplified Acute Physiology Score (< 55 or ≥ 55) [38]. Patients are assigned to treatment groups (citrate or heparin) using block randomization stratified by center. A comprehensive document describing the randomization procedure is kept in a confidential manner at the CIC-EC of Dijon.

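### Adjustment of the primary comparison is triggered by imbalance, although the trial minimises on known factors; a Cox model on those factors should be pre-specified instead

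*Protocol article*

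**What the plan says.** **Allocation** (Protocol article, Randomization procedure). "The allocation is based on a minimization technique taking into account the catheter insertion site (jugular or femoral), type of dialysis (continuous or intermittent"; the third factor is the "Simplified Acute Physiology Score (< 55 or ≥ 55". The same paragraph continues: "Patients are assigned to treatment groups (citrate or heparin) using block randomization stratified by center".

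**Baseline** (Baseline comparability). "The baseline characteristics of both groups will be compared by univariate analysis", by the usual two-sample tests.

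**Primary analysis** (Primary objective). "Event-free catheter survival will be compared between groups using the log rank test". No strata or covariates are named. A second step follows: "multiple Cox regression analysis will be performed as appropriate, to take into account any potential imbalances in potential confounders between groups". Scheduled catheter withdrawal and death are censored.

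None of the analysis sections (Baseline comparability, Primary objective, Secondary objectives) mentions the allocation factors.

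**The concern.** The trial takes care to balance three patient factors and centre, but the analysis makes no stated use of them. The only stated route to adjustment is imbalance. That route works against the design: minimisation is there to prevent imbalance on site, dialysis type and severity class, so these are the factors the trigger is least likely to bring in. Variables left to chance are the ones most likely to qualify.

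Two things are at stake. First, the adjusted hazard ratio would depend on what happened to differ in this sample and not on a model fixed beforehand. Second, if the allocation factors do affect catheter survival, a test that ignores them is conservative after minimisation and has less power than one that includes them.

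**Working it through.** **The plan's own figure.** The sample size section assumes a "median of 12 days in the citrate group versus nine days in the heparin group", with alpha 5% and power 80%. With exponential survival the hazard ratio is 9/12 = 0.75. Sidedness is not stated; two-sided is assumed.

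- Schoenfeld: events = 4 × (1.960 + 0.842)² / (ln 0.75)² ≈ 380. Freedman's formula gives 385.
- The stated 366 is slightly low: 366 events give 78.6% power and 386 give 80.7%.
- The inflation step reproduces: 366 / 0.95 = 385.3, hence 386.

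These powers assume that every patient has an event. Censoring lowers them whichever test is used, which is a separate matter from this point.

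**What adjustment changes.** Trials of 386 patients were simulated, 3,000 per cell.

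- From the article: N, the heparin median of nine days (hazard ln 2 / 9) and the hazard ratio of 0.75, applied here as a conditional effect.
- Assumed: four binary factors, each split about evenly (site, dialysis type, severity class, centre); minimisation on all four with a biased coin of 0.8; the first three prognostic, with the same hazard ratio each; censoring of none or about 30%.
- Compared: unadjusted log-rank against a Cox model with treatment and the four factors, two-sided 5%.

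Power at conditional hazard ratio 0.75:

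| Assumed HR per factor | No censoring: log-rank / Cox | Gain (points) | About 30% censored: log-rank / Cox | Gain (points) |
|---|---|---|---|---|
| 1.0 | 79.9% / 79.9% | 0.0 | 65.7% / 65.4% | −0.3 |
| 1.25 | 77.7% / 79.7% | 2.0 | 63.0% / 64.0% | 1.0 |
| 1.5 | 74.2% / 81.4% | 7.2 | 58.4% / 65.2% | 6.8 |
| 2.0 | 61.6% / 79.8% | 18.2 | 48.8% / 63.3% | 14.5 |

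Type I error of the unadjusted log-rank at factor hazard ratios 1.0, 1.25, 1.5 and 2.0 was 4.7%, 4.3%, 3.8% and 2.6% without censoring, and 5.1%, 4.6%, 3.4% and 3.4% with it. The adjusted Cox model gave 4.6% to 6.0% over the eight cells. The simulation standard error at 5% is √(0.05 × 0.95 / 3,000) = 0.4 points.

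**Against the planned effect.** The planning medians describe whole groups, so the planned effect is marginal. With the marginal hazard ratio held at 0.75 and no censoring, the unadjusted log-rank had 80%, 82% and 83% power at factor hazard ratios 1.25, 1.5 and 2.0. It does not fall short of the planned 80% because it is unadjusted.

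**A stratified log-rank as an alternative.** Crossing the three patient factors gives 8 cells; adding two centres gives 16.

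- Unadjusted against 8-cell stratified log-rank, no censoring: 79.0% against 75.9% at factor hazard ratio 1.0, and 76.7% against 75.6% at 1.25.
- With about 50% events: 52.5% against 49.8%, 48.5% against 46.5%, and at 1.5, 46.6% against 48.0%.
- A 16-cell version without censoring gave about 74%, where the adjusted Cox model gave 80-81%.

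Full stratification therefore loses power when the factors are weak.

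**The case against.** The strongest reply is that a plain log-rank fixed in advance is a legitimate primary test. Its type I error is not inflated, and the later Cox model cannot change its result. The article never calls the allocation factors prognostic for catheter survival, and severity may act mainly through death, which is censored. A condensed article may also leave strata and covariates to an analysis plan that is not shown.

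Much of this stands. It rules out several stronger conclusions that a reader might draw:

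- **That the primary test is invalid.** It is at or below 5% within simulation error.
- **That the unadjusted hazard ratio is biased.** A value nearer 1 than the conditional one reflects non-collapsibility: it estimates a different quantity.
- **That the trial misses its planned power for this reason.** The marginal-effect runs show otherwise.
- **That the baseline tests formally select the covariates.** The article gives imbalance as the reason for adjustment but does not tie it to those tests.
- **That the allocation is self-contradictory.** The two sentences are hard to reconcile as written, but they may condense minimisation within centre, and the article refers to a fuller confidential description.

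One part does not stand. The trigger is not a detail left for later. The article itself gives imbalance as the reason to adjust, and a covariate list elsewhere would not repair that reason.

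**Conclusion.** The concern holds as a matter of efficiency and pre-specification. The stated trigger tends to omit the factors on which the trial allocates and makes the adjusted hazard ratio depend on chance differences. No size can be read from the article, because it gives neither the prognostic strength of the factors nor the censoring rate. Under the assumptions shown, adjustment gains about 0 points of power at a per-factor hazard ratio of 1.0, 1-2 at 1.25, 7 at 1.5 and 15-18 at 2.0, for a fixed conditional hazard ratio of 0.75. Adjustment therefore costs next to nothing if the factors are unimportant and helps materially if they matter.

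**What to change.** 1. Make the primary analysis a Cox model with treatment, catheter site, dialysis type and severity score class, with centre as covariate or stratum, fixed whatever the observed balance.
2. Keep the unadjusted log-rank as supportive. Report the unadjusted hazard ratio beside the adjusted one, because the adjusted one is conditional on these factors.
3. Remove imbalance as the reason for adjusting, and give the baseline comparisons no role in choosing covariates.
4. Do not replace the model with a log-rank stratified on all 8 to 16 cells.
5. Reconcile the two allocation sentences, for example by stating whether minimisation is run with centre as a factor or within centre, so that the model matches the algorithm used.

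The cost is wording: the factors are known at randomisation, and no patients or data are added. The price is a conditional hazard ratio, which item 2 covers. The change should be dated before any unblinded comparison. The article reports 191 patients recruited and an interim look after 200, and that look also names the log-rank test, so the plan should say which test applies there.

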#### Study treatments

Citrate or heparin, according to the study group, will be instilled into each lumen of the catheter to attain a total volume corresponding to the volume of each branch according to the Summary of Product Characteristics. Before each administration of citrate or heparin, the catheter lumens will be flushed with 10 mL of saline as quickly as possible. Then, the lock solution (heparin or citrate) will be injected slowly (over at least 10 seconds duration) into each lumen.

Before initiation of RRT and use of the catheter, a minimum of 5 cc of liquid will be extracted from each lumen (volume greater than the contents of each lumen). Catheter patency will be verified by performing a blood return with a 20 cc syringe. If the 20 cc syringe fills smoothly in under four seconds, this corresponds to a blood flow of 300 mL/min on the hemodialysis machine. All catheters used will have a minimum diameter of 13.5 French. Only one catheter per patient will be considered for the study analysis.

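### The analysis labelled per-protocol is as-treated: if heparin patients who switch lock are counted as citrate from randomization, it leans modestly towards citrate

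*Protocol article*

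**What the plan says.** All of the following is from the protocol article.

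- **Primary objective, primary analysis:** "The primary analysis will be on an intention-to-treat basis", by log-rank test and then Cox regression. "Time zero is defined as the time of randomization".
- **Primary objective, censoring:** "Patients will be censored in case of scheduled withdrawal of the catheter, or death". A change of lock is not listed.
- **Primary objective, supportive analysis:** "A per-protocol analysis will also be performed, using the same techniques", followed by the grouping rule: "For the per-protocol analysis, patients will be grouped according to the treatment actually received".
- **Sample size calculation:** the sample is enlarged for "possible crossovers between groups (less than 5% switching from heparin to citrate) due to heparin-induced thrombocytopenia". No crossover in the other direction is mentioned.
- **Study treatments:** "Only one catheter per patient will be considered for the study analysis". The primary endpoint makes it the first one.
- **Exclusion criteria:** documented or suspected HIT is an exclusion, so a switch for HIT can only follow a diagnosis made after entry.

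The article does not say which group a patient belongs to after receiving heparin first and citrate later on the same catheter.

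**The concern.** A per-protocol analysis keeps patients in their randomized arm and restricts to those who adhered. Grouping by what was received is a different analysis, usually called as-treated, and it gives up the protection of randomization.

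Here the difference has a direction. A heparin patient can move to citrate during the analysed catheter only if that catheter has not yet been withdrawn. If the patient is then counted as citrate from randomization, the days before the switch are immortal time: no event could have occurred in them, and they were spent on heparin. The citrate group gains a long-surviving catheter and the heparin group loses one. Because the foreseen crossover is one-way, nothing offsets this.

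The error favours citrate, which is the trial's superiority hypothesis. A supportive analysis that leans that way is a poor check on the intention-to-treat result.

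**Working it through.** **Plan figures used.** The article gives no figure for this analysis, so there is none to reproduce. Its allowance for crossover and loss does reproduce: 366 / (1 − 0.05) = 385.3, rounded up to 386, or 193 per group. The planned effect is 9 / 12 = 0.75. Five per cent of 193 is 9.65 heparin patients, so about ten switchers is the ceiling.

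**Assumptions not in the documents.** Exponential catheter survival; switching unrelated to prognosis among those still at risk; a switch window of days 2–5, 5–10 or 7–14. The main case has no competing removal or death.

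**Arithmetic with no treatment effect** (median 9 days in both arms):

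- Event hazard λ = ln 2 / 9 = 0.0770 per day; mean catheter time 1/λ = 12.98 days.
- Each randomized arm: 193 events in 193 × 12.98 = 2,506 catheter days.
- A switcher on day s contributes s + 12.98 days on average and one event. Take the mid-window day, s = 7.5, giving 20.48 days; 9.65 switchers carry 197.7 days.
- Citrate as received: (193 + 9.65) / (2,506 + 197.7) = 202.65 / 2,703.7 = 0.0750 per day.
- Heparin as received: (193 − 9.65) / (2,506 − 197.7) = 183.35 / 2,308.3 = 0.0794 per day.
- Rate ratio = 0.0750 / 0.0794 = 0.94, where the truth is 1.00.

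The same steps with s = 3.5 and s = 10.5 give 0.97 and 0.92.

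**Simulation** (3,000 runs per scenario, 193 per arm, no true effect, no competing removal, 5% of heparin patients switching):

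| Switch window | Mean HR, as received from day 0 | Log-rank rejection at nominal 5% | Rejection favouring citrate |
|---|---|---|---|
| Days 2–5 | 0.97 | 6.3% | 5.1% |
| Days 5–10 | 0.94 | 9.1% | 8.6% |
| Days 7–14 | 0.93 | 12.4% | 11.9% |

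Across the three windows, 2.5% switching gives mean HRs of 0.99 to 0.96, and 1% gives 0.996 to 0.98.

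**Competing removal or death.** With a censoring hazard equal to the event hazard (0.077 per day) and 5% switching, the mean HRs are 0.95, 0.91 and 0.87, with rejection in 6.3%, 10.1% and 16.9% of runs. The intention-to-treat HR in those runs averaged 1.00 to 1.02. An assumed 0.065 per day also goes down to about 0.87 for late switches near the ceiling.

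**Under the planned effect** (9 versus 12 days, 5% switching, no competing removal), the as-received HR is 0.73 to 0.70 against a true 0.75; intention-to-treat gives about 0.76.

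**Alternatives.** In the null runs without competing removal, keeping randomized arms and censoring at the switch gives HR 1.00 and about 5% rejection. A time-dependent lock covariate also gives HR 1.00 (1,000 runs per scenario).

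**The case against.** **Day-0 crediting is inferred.** A reader might take the article to say that switchers are credited to citrate from randomization. It does not. Grouping by first lock received would give the intention-to-treat grouping for these patients, with no immortal time. Excluding mixed exposure or splitting follow-up is also conceivable, and such detail may sit in an analysis plan that is not shown. This stands, so the bias has to be stated conditionally. It does not remove the point: the grouping rule itself is stated, it is not per-protocol, and under a first-lock reading it would change nothing for the only crossover foreseen.

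**A reader might infer that this analysis could overturn or rescue the primary result.** The documents do not support that. Intention-to-treat is primary, and nothing lets the supportive analysis override it.

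**The size rests on assumptions.** This stands. The documents give no switch timing or competing hazard, and 5% is a ceiling. Only switches during the first catheter matter.

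**HIT may itself raise later catheter failure.** Then the distortion shrinks, and the right comparator is no longer 1.00. With a doubled later hazard and 4.9% switching, intention-to-treat is 0.97 and as-received 0.93 with competing removal, or 0.976 and 0.967 without. Only about 0.01 to 0.04 is then due to the grouping.

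**Censoring at a switch for HIT can be informative.** This also stands. In that same scenario it moves the estimate from about 0.97 to 1.00, removing a real consequence of assignment to heparin.

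**Conclusion.** The point holds in a limited form. The label and the rule disagree: the analysis is as-treated. Under the natural reading, which the article does not spell out, it favours citrate. With no true effect and 1% to just under 5% of heparin patients switching, the expected HR is roughly 0.92 to 0.99, or as low as about 0.87 with late switches and heavy competing removal. Near the ceiling, a nominal 5% test can reject more than twice as often as it should.

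These figures depend on the assumed switch windows, exponential survival and competing hazard, and they shrink if HIT raises later failure. The intention-to-treat analysis is unaffected, and even the lowest of these values is well short of 0.75. The text should be corrected because the remedy is cheap, but the trial's main conclusion does not hang on it.

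**What to change.** Replace the grouping sentence with one of these:

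1. **Per-protocol proper:** include patients without major deviation, analyse them in their randomized arm, and censor follow-up at any switch of lock. State that this censoring may be informative and add a sensitivity analysis, for example with inverse-probability-of-censoring weights.
2. **As-treated, so named:** enter lock in the Cox model as a time-dependent covariate, so that days before a switch count as heparin and days after it as citrate.

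Either version also settles where a patient who received both locks belongs. It should be fixed before unblinding. The cost is one sentence, the switch dates of at most about ten patients, and, for the first option, slightly less follow-up.
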